# The LEAD study protocol: a mixed-method cohort study evaluating the lung cancer diagnostic and pre-treatment pathways of patients from Culturally and Linguistically Diverse (CALD) backgrounds compared to patients from Anglo-Australian backgrounds

**DOI:** 10.1186/s12885-018-4671-4

**Published:** 2018-07-21

**Keywords:** Lung cancer, Ethnicity, Time intervals, Cancer diagnostic pathway

## Abstract

**Background:**

Lung cancer is the leading cause of cancer mortality worldwide. Early diagnosis and treatment is a key factor in reducing mortality and improving patient outcomes. To achieve this, it is important to understand the diagnostic pathways of cancer patients. Patients from Culturally and Linguistically Diverse (CALD) are a vulnerable group for lung cancer with higher mortality rates than Caucasian patients. The aim of this study is to explore differences in the lung cancer diagnostic pathways between CALD and Anglo-Australian patients and factors underlying these differences.

**Methods:**

This is a prospective, observational cohort study using a mixed-method approach. Quantitative data regarding time intervals in the lung cancer diagnostic pathways will be gathered via patient surveys, General practitioner (GP) review of general practice records, and case-note analysis of hospital records. Qualitative data will be gathered via structured interviews with lung cancer patients, GPs, and hospital specialists. The study will be conducted in five study sites across three states in Australia. Anglo-Australian patients and patients from five CALD groups (i.e., Arabic, Chinese, Greek, Italian and Vietnamese communities) will mainly be identified through the list of new cases presented at lung multidisciplinary team meetings. For the quantitative component, it is anticipated that 724 patients (362 Anglo-Australian and 362 CALD patients) will be recruited to obtain a final sample of 290 (145 per group) assuming a 50% patient survey completion rate and a 80% GP record review completion rate. For the qualitative component, 60 interviews with lung cancer patients (10 Anglo-Australian and 10 patients per CALD group), 20 interviews with GPs, and 20 interviews with specialists will be conducted.

**Discussion:**

This is the first Australian study to compare the time intervals along the lung cancer diagnostic pathway between CALD and Anglo-Australian patients. The study will also explore the underlying patient, healthcare provider, and health system factors that influence the time intervals in the two groups. This information will improve our understanding of the effect of ethnicity on health outcomes among lung cancer patients and will inform future interventions aimed at early diagnosis and treatment for lung cancer, particularly patients from CALD backgrounds.

**Trial registration:**

The project was retrospectively registered with Australian New Zealand Clinical Trials Registry (registration number: ACTRN12617000957392, date registered: 4th July 2017).

## Background

Lung cancer is the most common cancer worldwide. In 2012, it was estimated that there were 1.8 million new cases of lung cancer, accounting for 13% of all incident cancer cases [1]. Lung cancer is also the leading cause of cancer mortality, estimated to be responsible for 1.59 million (or 19.4% of the total) cancer deaths in 2012 [1]. One reason for this high mortality rate is that lung cancer is often diagnosed at a late stage, which is associated with higher mortality than early-stage disease [2–5]. Walters et al. (2013) analysed population-based data of lung cancer between 2004 and 2007 in six developed countries (including Australia, Canada, Denmark, Norway, Sweden and the UK) and found that at least half of lung cancer patients were diagnosed at a late stage when curative treatment is unlikely as an option.

Early diagnosis and treatment is considered a key factor in reducing lung cancer mortality and improving patient outcomes [6]. When cancer patients are diagnosed early, they are more likely to be suitable for curative treatment, leading to a greater probability of survival, less morbidity, and improved quality of life [7]. To achieve early diagnosis and treatment, it is important to understand the diagnostic and treatment pathways of cancer patients in order to inform the development of interventions to reduce diagnostic and treatment delay [6, 8]. Guided by the Model of Pathways to Treatment [8], the LEAD project (Lung cancer diagnostic and treatment pathways: a comparison between Culturally and linguistically diverse [CALD] and Anglo-Australian patients) will use a mixed-method, observational cohort design to explore the pathways to diagnosis and pre-treatment of lung cancer patients in multicultural Australia.

### Lung cancer among the CALD population

The LEAD project focuses on these differences, because there is evidence suggesting that compared to Caucasian lung cancer patients, CALD patients are a vulnerable group, with poorer survival rates and a lower likelihood of receiving timely and appropriate treatment [9–12]. Possible reasons for these poorer outcomes include more advanced stage at diagnosis, cultural beliefs towards treatment, fatalism and medical mistrust [10, 13, 14].

Similar to many Western countries, people from CALD backgrounds account for a significant proportion of Australia’s population. Data from the most recent census shows that in 2016, Australia’s population consisted of people from over 300 ethnic groups with more than a quarter (26%) born overseas and a further one-fifth (20%) having at least one overseas-born parent [15]. This cultural diversity has been reflected in lung cancer patients. A recent retrospective cohort study with six public and two private hospitals in Victoria Australia found that, of the 1417 patients diagnosed with lung cancer between 2011 and 2014, 51% were born overseas [16].

However, most of current research with the CALD population has been conducted in the United States (US). Given the significant differences in the healthcare system and the composition of the CALD communities between Australia and the US (for example, the top three countries of birth for the overseas-born population in 2016 were England, New Zealand, and China for Australia [Australian Bureau of Statistics, 2017], and Mexico, China and India for the US [Migration Policy Institute, 2018]), it is important to explore whether the finding of poorer outcomes among CALD lung cancer patients in the US studies also applies to the Australian context.

### Model of Pathways to Treatment

The diagnostic and treatment pathway of lung cancer patients is complex, comprising multiple stages from patients noticing symptoms and seeking help from health professionals, to obtaining a formal diagnosis and starting treatment [6]. It is, therefore, useful to apply a theoretical model in cancer pathway studies to inform the description and measurement of the stages along this pathway [6].

The Model of Pathways to Treatment [8] will be used in the LEAD project as the theoretical model to understand and measure the cancer diagnostic and pre-treatment pathway. This model is built on the findings from a systematic review and has been incorporated into the Aarhus Statement, an international guideline for the design and reporting of studies on early cancer diagnosis [6]. An important feature of this model is that it uses events that can be readily understood by patients, clinicians and researchers to define the key time intervals underlying this pathway [8]. As shown in Fig. 1, these intervals are: (1) the appraisal interval (time between first detection or awareness of a symptom to recognising a need to discuss the symptom with a healthcare professional), (2) the help-seeking interval (time from recognising the need to discuss their symptoms to attending the first consultation with a healthcare professional); (3) the diagnostic interval (time from first consultation to a formal cancer diagnosis), and (4) the pre-treatment interval (time from the formal diagnosis to initiation of treatment) [8].

**Fig. 1 Fig1:**
[figure not shown]
Model of Pathways to Treatment [8]. HCP: health care provider

Another important feature of this model is that it considers and categorises factors that are likely to have important impacts on these time intervals. These include: (1) patient factors (e.g. demographic, co-morbidities, and cultural factors), (2) healthcare provider and system factors (e.g. access, healthcare policy), and (3) disease factors (e.g., site, size) [8]. This framework facilitates a systematic investigation of the enablers and barriers that are encountered along the cancer diagnostic and pre-treatment pathway.

### Study aims

The two aims of the LEAD project are (1) to explore the differences in the four time intervals along the lung cancer diagnostic pathway between CALD and Anglo-Australian patients, and (2) to explore patient, health care provider, and health system factors that are associated with the differences in time intervals between the two groups. Based on earlier studies, we hypothesise that CALD patients will report longer time intervals than Anglo-Australian patients. There is no specific hypothesis associated with the second research aim because it is exploratory in nature.

## Methods/Design

### Study design and setting

LEAD is a prospective, observational cohort study using a mixed-method approach to gather and interpret quantitative and qualitative data. Quantitative information on time intervals (see Fig. 2) and other factors will be gathered via patient survey, GP review of general practice records, and case-note analysis of hospital records. Qualitative information will be gathered via structured interviews with lung cancer patients, general practitioners (GPs), and hospital specialists.

**Fig. 2 Fig2:**
[figure not shown]
Study design of the LEAD. GP: General Practitioner

The LEAD project will be conducted in five sites across three states in Australia: three Integrated Cancer Services in Melbourne, Victoria; one public hospital in Sydney, New South Wales; and, one public hospital in Brisbane, Queensland. These health services provide coverage for all of metropolitan regions of Melbourne, Sydney and Brisbane and include significant numbers of lung cancer patients, including CALD patients.

### Participants and recruitment

Three groups of participants will be recruited for this study: lung cancer patients, GPs and hospital specialists.

#### Lung cancer patients

Lung cancer patients will be involved in both the quantitative and the qualitative components of LEAD. The quantitative component involves a patient survey and a case-note analysis of hospital records. The qualitative component involves an interview. The patient eligibility criteria are: (1) have a diagnosis of primary lung cancer at the study sites within the past month or during the recruitment phase, and (2) be of CALD or Anglo-Australian descent. We will use prospective recruitment and also include patients who have been diagnosed within the past month to minimise the risk of recall bias and participant attrition due to death or terminal illness.

Patients of CALD descent are defined in the study as those who were born overseas and from one of the following ethnic groups: Arabic, Chinese, Greek, Italian, and Vietnamese. These are the most common ethnic groups for overseas-born people in Australia [15]. Anglo-Australian patients will be defined as those who were born in Australia or other major English-speaking countries (Canada, New Zealand, the United Kingdom, and the US). Patients who are pregnant or aged under 18 years will be excluded from the study because lung cancer among these two groups is very uncommon and those patients tend to have a different diagnostic pathway to the general population [17, 18].

Eligible patients will be identified through the list of new cases presented at the respective lung multidisciplinary team meetings. Additional recruitment sources, such as the bronchoscopy lists, might be used for some study sites on a local basis. The project coordinators will regularly go through these lists throughout the recruitment phase or until the required sample size has been reached.

After an eligible patient has been identified, the site coordinator will send a letter to invite the patient to participate in the patient survey and the patient interview. Patients may consent to take part in either or both activities. A waiver of consent has been obtained for the case-note analysis of hospital records, and the required data will be gathered by a hospital staff member with authorised access to medical records.

The invitation letter will be sent together with the patient survey and a reply-paid envelope. Two weeks after the initial invitation, the patients will receive a reminder phone call and a reminder letter from the site coordinator. For CALD patients, the invitation letter and the survey will be provided in English as well as their preferred languages. As an incentive to take part in the interview, the patients will be offered a $40 gift card, in line with the average hourly Australian wage.

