## Discussion

The LEAD project is the first Australian study to compare the time intervals along the lung cancer diagnostic pathway between CALD and Anglo-Australian patients. The project will also explore the underlying patient, healthcare provider, and health system factors that influence the time intervals in the two groups. This information will improve our understanding of the effect of cultural diversity on health outcomes among lung cancer patients and will inform future interventions aimed at early diagnosis and treatment for lung cancer, particularly patients from CALD backgrounds.

There are a number of strengths in the design of the LEAD study that could be considered in future studies. Firstly, the Model of Pathways to Treatment (Walter et al., 2012) will be used to conceptualise and measure the various stages along the cancer diagnostic pathway. This model provides clear definitions and measurements of time intervals along the cancer diagnostic pathway and has been incorporated into the Aarhus Statement, an international guideline for the design and reporting of studies on early cancer diagnosis [6]. The adoption of such a model enables a systematic approach in data collection and allows data comparison between studies and across cancer types.

Secondly, the study will use both quantitative and qualitative methods and will collect information from multiple groups, including lung cancer patients, GPs and specialists. The inclusion of these different methods and participant groups is particularly important given the complexity of the cancer diagnostic and pre-treatment pathway. Compared to earlier studies where a single research method or participant group was used [e.g. 10, 13], such an approach enables a more comprehensive picture of the diagnostic pathway.

Thirdly, the study includes both CALD and Anglo-Australian patients. As noted in a systematic review of cancer beliefs in CALD populations, one limitation of current studies in this area is that few have comparator groups of the local population, making it difficult to disentangle local- versus ethnicity-specific factors in these studies [14]. Compared to these studies, the inclusion of both groups in our study enables a direct comparison between the two groups, leading to a deeper understanding of cultural differences in the diagnostic pathways.

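### The Anglo-Australian and CALD definitions are not mutually exclusive, and the comparator's birthplace-only rule does not match the descent criterion it is meant to implement

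*Protocol article*

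**What the plan says.** All the relevant rules stand in the protocol article under Participants and recruitment, Lung cancer patients.

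- The second eligibility criterion is that a patient "be of CALD or Anglo-Australian descent".
- CALD patients are "those who were born overseas and from one of the following ethnic groups: Arabic, Chinese, Greek, Italian, and Vietnamese". Two conditions must both hold.
- For the comparator, "Anglo-Australian patients will be defined as those who were born in Australia or other major English-speaking countries". The countries listed besides Australia are Canada, New Zealand, the UK and the US. Country of birth is the only condition.

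The article gives no order of precedence between the definitions and does not say how Australian-born patients of the five ethnicities are handled. Under Study aims, "we hypothesise that CALD patients will report longer time intervals than Anglo-Australian patients". The Discussion names the comparator as a strength because "the inclusion of both groups in our study enables a direct comparison between the two groups, leading to a deeper understanding of cultural differences".

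**The concern.** The two groups are built on different criteria: birthplace and ethnicity for one, birthplace alone for the other. Two separate problems follow.

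1. **Overlap.** A patient of, say, Chinese or Greek ethnicity born in New Zealand or the UK is overseas-born and of a listed ethnicity, and was also born in a listed English-speaking country. Both definitions are met.
2. **Placement in the comparator.** An Australian-born patient of a listed ethnicity is not overseas-born, so cannot be CALD, but satisfies the Anglo-Australian definition in full. This is not overlap. It is a mismatch with the descent criterion, because birthplace does not measure descent.

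Group membership is the exposure in the log-rank comparison of each interval. A comparator that can include the five ethnicities is a weaker basis for the cultural contrast the Discussion claims. If these patients' intervals lie nearer to the CALD group's, the observed difference shrinks and power falls.

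**Working it through.** **Applying the definitions as written to a patient of one of the five ethnicities**

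| Born in | Meets CALD? | Meets Anglo-Australian? |
|---|---|---|
| Australia | No | Yes |
| Canada, New Zealand, UK or US | Yes | Yes |
| Any other country | Yes | No |

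Only the last row gives a placement that is both unique and consistent with descent. This step needs no assumption.

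**Reproducing the planned sample size**

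Inputs from Statistical Considerations: medians of 60 and 88 days, two-sided alpha 0.05, 90% power, log-rank test, 145 per group. I assume exponential times and an event for every patient.

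- Hazard ratio (HR) = 60/88 = 0.682; its logarithm is −0.383.
- Schoenfeld events = 4 × (1.960 + 1.282)² / 0.383² = 287.
- Freedman events = (1.960 + 1.282)² × [(1 + 0.682)/(1 − 0.682)]² = 294.
- Schoenfeld power with 290 events = 0.903.

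The stated 290 reproduces. The sample size arithmetic is not at fault.

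**Dilution**

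Let a share q of the comparator have a median of m days, the remainder 60 days, and the CALD group 88 days. The documents do not give q or m, so both are assumed. With 145 in the group, q of 5%, 10% and 20% is about 7, 15 and 29 patients (145 × q).

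Two values of m are used: 88 days (fully CALD-like) and 74 days (halfway, (60 + 88)/2). The comparator median solves (1 − q)·2^(−t/60) + q·2^(−t/m) = 0.5. Power comes from simulated log-rank tests at 145 per group. The HR is the large-sample Cox value.

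| q | Median difference, m = 88 | HR, m = 88 | Power, m = 88 | Power, m = 74 |
|---|---|---|---|---|
| 0% | 28.0 days | 0.68 | 90% | 90% |
| 5% | 26.9 days | 0.70 | about 86% | about 88% |
| 10% | 25.8 days | 0.72 | 80–82% | about 86% |
| 20% | 23.5 days | 0.75 | about 69% | about 81% |

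The range at 10% is the spread between separate simulation runs. A closed-form Schoenfeld calculation on the ratio of medians gives somewhat higher power at m = 88 (87%, 84% and 75%), because the diluted comparator no longer has proportional hazards against the CALD group. The simulated figures are the better guide.

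**The case against.** **Overseas birth is a deliberate part of the CALD definition.** Keeping Australian-born patients out of CALD follows from it, and how to treat the second generation is a design choice. That stands. But leaving them out of CALD does not require putting them in the comparator, and the birthplace rule does so by default.

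**The descent criterion could be read as a further filter**, so that an Australian-born patient of Vietnamese family would not qualify at all. That reading is possible. However, the article goes on to define Anglo-Australian by birthplace, so the criterion and its definition give different answers for the same patient. It is therefore not certain that all such patients would enter the comparator.

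**A condensed article may leave classification procedure to the full protocol.** This is fair for procedure, and for that reason the article does not show that sites decide case by case. But it states both definitions explicitly, and as stated they overlap.

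**Modest dilution costs little.** This also stands. Nothing in the documents says that people born in an English-speaking country have the intervals of overseas-born CALD patients. Some of the study's CALD provisions, such as translated surveys and interpreters, concern language, which may matter less for them.

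Three stronger readings are tempting and not supported:

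- That every interval contrast is biased toward no difference. This requires the hypothesis to be true for each interval and the patients in question to resemble the CALD group.
- That about one-fifth of the comparator is affected. The census figure, "a further one-fifth (20%) having at least one overseas-born parent", covers the whole population and parents from any overseas country, so it does not estimate the share of five ethnicities among lung cancer patients.
- That the overlap itself causes the dilution. True overlap concerns only those born in the four overseas English-speaking countries. The Australian-born are a separate and probably larger group.

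**Conclusion.** The point holds as a defect in the stated exposure definition. The groups are not mutually exclusive, and the Anglo-Australian definition does not implement the descent criterion. Both can be read directly from the text.

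The effect on power is conditional. For an assumed 5% to 20% of the comparator, power falls from 90% to between about 86% and 69% if these patients have the full CALD median, and to between about 88% and 81% if their median lies halfway. The first range is the worst case of the two considered. Both rest on exponential times, complete follow-up to the event and the planning medians, and the true share is unknown.

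**What to change.** - Add to the Anglo-Australian definition that the patient is not from any of the five listed ethnic groups.
- State that an overseas-born patient of a listed ethnicity is always CALD, whatever the country of birth.
- Keep Australian-born patients of the five ethnicities out of the primary comparator, either excluded or reported separately, and add a sensitivity analysis that includes them.
- Record ethnicity at screening or in the survey. Because the survey may be completed anonymously, later recovery from medical records cannot be relied on.

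No home-language condition is needed to make the groups exclusive, and adding one would narrow the comparator on a debatable ground.

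The cost is slightly fewer eligible comparators and one demographic item. The study was registered retrospectively in July 2017, before the article appeared, so recruitment may already have begun. The rule would then have to be applied at analysis to patients already recruited, as far as their ethnicity is known.

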#### GPs

The GP of enrolled lung cancer patients will be invited to take part in LEAD. Their involvement in the quantitative component will be in the form of a review of their general practice records, and their involvement in the qualitative component will be in the form of an interview. The GP will be identified by the patients who have chosen to participate in the study and who have provided consent for the research team to access their hospital and general practice medical records (see Fig. 3).

